### Inclusion criteria

All persons residing in the area in possession of a valid national identification card attending the local clinics who are aged 18 and above and are able to give written informed consent will be eligible for enrolment if they score above the pre-determined cut-off point (≥9) on the SSQ-14 [15].

### Exclusion criteria

All persons who are unable to comprehend the nature of the study in either English or *Shona* (local language), have suicidal intent, end stage AIDS, are currently in psychiatric care, present with current psychosis, intoxication, and/or dementia will be excluded. All those excluded for medical reasons will be referred for appropriate care to one of two tertiary facilities in Harare. Those reported to be physically unwell by the clinic Nurse-in-Charge will be excluded. Pregnant women in the third trimester and women within the 3-months post delivery period will be excluded. All those not residing in the geographical locality or whose address can not be verified through the clinics’ registry will also be excluded.

To ensure that all clinic attendees have an equal chance of being selected, three participants will be recruited per weekday in those clinics that have fixed days allocated for specific medical conditions such as HIV/AIDS, diabetes, hypertension. In clinics with no such medical condition-based services we will recruit participants until our total of 24 per site is reached, ensuring that the corresponding strata in the control sites receive the same approach.

### Sample size

The sample size of 24 clusters, each with 24 participants enrolled provides 80% power to detect an effect size of 0.75, assuming a coefficient of variation (k) = 0.2 and 20% loss to follow-up. We would have 90% power to detect this effect size if the coefficient of variation is smaller (k = 0.16), and 90% power to detect a larger effect size of 0.85 if k = 0.19. The coefficient of variation is defined as the between-cluster variation divided by the mean value, for the outcome of interest (mean SSQ score). In the absence of this measure for each clinic, we based this on the value of k for HIV prevalence. The effect size is based on a recent systematic review, which identified six intervention trials of lay-health worker (LHW) led interventions with severity of CMD as an outcome [4]. The pooled effect size for the LHW intervention vs. control at 6 months was 0.75 (95% CI 0.21–1.29) [4].

### Intervention

The intervention consists of six sessions of a PST package which is delivered on a bench in a discrete area outside of the local clinic [11]. Each session will last approximately 30–45 min with the first session lasting up to an hour (Table 1). The 6 sessions will be completed within a 4–6 week period. Supervisors will not be present during the actual sessions but they will have access to the audio-recording after each session. All sessions will be audio recorded for fidelity, with fidelity being assessed using a checklist to ensure that the LHW has covered all the critical PST components. The fidelity assessment will be carried out by the study clinicians, which include psychiatrists and clinical psychologists. LHWs will have access to immediate support through either their immediate supervisor who will be available at clinic level should the LHW require assistance during a session, a study clinical psychologist, the study coordinator or through the use of a mobile phone device to enable instant communication with team members when nobody is available at clinic level. The psychological approach is based on providing psycho-education (information, advice and support) together with a problem-solving module that includes a component of positive activity scheduling (behavioural activation). In addition, patients will receive up to 6 brief text messages and/or calls reinforcing the PST approach and encouraging adherence to treatment as our survey of patients utilizing primary health facilities indicates that over 90% possess a mobile phone. The small proportion of participants who are recruited for the study but have no mobile phone will be asked to provide a mobile phone of an alternative relative or friend. These text messages will be sent to participants who attend less than 3 sessions or those who the LHW and supervisor feel need extra support. Text messages will be sent out once a week. Whenever necessary LHWs will be encouraged to act as facilitators to help patients to get access to other sources of support using their mobile devices. The income generating component will be open to all persons assigned to the intervention arm if they chose to after receiving a minimum of four sessions of the PST. This income generating component will focus on group peer support and sharing while actively crocheting a shopping bag from recycled plastic materials, the latter being a skill that can generate income for the participants. This forum will give participants an opportunity to learn through behaviour activation.

**Table 1 Tab1:** Description of the problem solving therapy intervention

Theoretical basis	Cognitive behavioural therapy
Delivering agent	Lay health workers (Health promoters). Mean age 58, all female, mean years of education 8, previous training in home based care for people living with HIV & AIDS, in community follow-up of persons on TB treatment and in delivering community health education and promotion e.g., through encouraging immunisation and methods to control disease outbreaks
Structure of intervention	Six weekly sessions of 30–45 min delivered through the Friendship Bench over 6 weeks, including home visits where deemed necessary. The first session lasting between 45 and 60 min
Structure of sessions and areas covered	*Part 1*. **Problem identification (Kuvhura pfungwa)**: (A) Share Shona Symptom Questionnaire (SSQ) information with client, explain symptoms in relation to *kufungisisa*, (B) Actively listen to clients story, identify and list problems raised, clearly define problem/s. **Problem exploration (kusimudzira)**: (C) understand the story, help client prioritise problems by summarizing and asking if you have missed anything, (D) brainstorm practical/feasible solutions, outline the options available (*these have to come from client*), encourage client to think over solutions of each problem before having the client decide which one to focus on. Help client to come up with a specific, measurable, achievable and realistic solution (*don’t tell client what to do*). Agree what the client will do before you next meet and set appointment date *Part 2*. **Reassure** **(Kusimbisa)** (E) Home visit if needed before second meeting, otherwise see again on the bench, how did it go? Went well, then reassure praise encourage. If no progress or new obstacles present then go back to Part 1 contents, redefine problem and goals, what were the obstacles? Problem solve around obstacles and give homework again and reassure, you can phone or send SMS to reassure client *(up to 6 per client).* *Part 3* **(kusimbisisa)**. (F) Summarise session 1, how did it go? Going well then reassure and ecourage. Still having problems with agreed plan? Go back to Part 1 again or if you feel frustrated go to supervisor
Remember	**Action plan: (**G) Zero in on a specific solution, focus on what client wants to do and *not what you think should be done*, (H) How, when, what assistance is needed? Referral if necessary (I). Identify activities the person used to find rewarding and which matter to them and encourage these (J), **Implementation:** (K) How will it be done? Motivate; homework, Refer after 4th session to support group. **Follow up: (**L) What has been achieved? What were/are the obstacles if any? Go back to Part 1 as often as needed during the 6 sessions (M) Reinforce. What has been achieved, repeat SSQ score. (N) No improvement refer to supervisor. nurse counsellor
Tools	SSQ-14, Friendship bench manual, referral protocol
Supervision	Weekly group supervision by a clinician (Psychologist) or senior study team member trained in PST. Access to direct mobile voice call to support team

LHWs will receive supervision and support from the clinical team at site level or through mobile phones using voice calls, and where necessary SMS messaging. The supervision will be for critical cases such as those with suicidal ideation who may need the input of a psychiatrist/psychologist and or medication. The SMS messaging/voice call will also be sent by the LHW to the participant particularly in cases where a participant has not turned up for a session on the bench and where challenges such as being unable to contact participant are encountered the project coordinators with the LHW will follow up with a voice call and if this yields no results a physical home visit will be carried out by the two. The support structure is based on a pre-determined algorithm developed during the formative research. This consists of study screen tool cut-off scores, criteria for referral including assessment for “red flags” clients who are suicidal and procedure immediate referral to a tertiary facility.

The control group will receive enhanced usual care (EUC) care through the clinic which will include psychoeducation on CMD, medication if indicated and/or referral to a psychiatric facility as part of usual standard procedure when clinic staff are unable to manage serious CMD cases. Participants will also receive between 2 and 3 supportive SMS messages or voice calls with the last SMS message or voice call being a reminder to attend the 6-months assessment.

### Data management

Data will be collected using tablet computers, all data is consecutively uploaded to a cloud enabling easy data handling for statistic purposes. The computing system is password protected, encrypted and only accessible to authorised study team members, any access to the system is automatically recorded. Data will be managed according to International Conference on Harmonisation guidelines for Good Clinical Practices. Participants will receive a unique study identification number recorded on all forms. Numbers will be maintained by the Project Director on a password protected, secure computer. Data will be entered into a password-protected database with independent double-data entry and a third person to resolve discrepancies. To minimize errors, range checks and skip patterns within data entry screens will be used. Database files will be exported in SAS format for bi-weekly batch error checking, monthly reporting and analysis. Data will be backed-up on an external hard-drive weekly. Recorded tapes will be transcribed into electronic records which will be backed-up on an external hard-drive after each session. All data will be kept confidential, under lock-and-key, accessible only to trained study staff. Participants’ data will be identified by an ID number only, and a link between names and ID numbers will be kept separately under lock-and-key.

### Data analysis

Data will be exported to Stata 13.1 for analysis. Baseline comparability will be assessed for individuals who did not consent to be part of the trial, and of participants who did not complete outcome assessments. Comparability of participants in the two arms will be assessed for potential confounding factors, notably: age, sex, HIV status and SSQ score. Due to the relatively small number of clusters, analyses will be based on cluster-level summary measures, as individual-level regression methods do not perform robustly when there are relatively few clusters per arm, especially for stratified cluster randomized trials [19]. For the primary outcome (SSQ score), the mean SSQ score for each cluster will be calculated and shown by strata and arm. The arithmetic mean and SD of these mean scores and associated 95% CI will be estimated by arm. Linear regression of the mean score on strata and arm (2-way analysis of variance (ANOVA) on arm and strata) will be used to estimate the difference in SSQ score and 95% CI associated with the intervention. For the binary outcome (proportion with depression), the risk for each cluster will be calculated, and shown by strata and arm. The mean and SD of the log risk will be used to estimate the geometric mean and associated 95% CI for each arm of the study. Linear regression of the log mean risk on strata and arm will be used to estimate the risk ratio and 95% CI. Linear regression of the mean risk on strata and arm will be used to estimate the risk difference and 95% CI. The approximate variance for the mean risks will be obtained based on the residual mean square from a 2-way ANOVA on arm and strata. A 95% CI for this will be calculated from the variance using a t-statistic with 18 degrees of freedom. Pre-defined sensitivity analyses includes adjustment for baseline SSQ score and other factors with imbalance (e.g. age, sex, HIV prevalence). We will also include tests for effect-modification by gender and other key factors.

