**Methods:**

Each of 24 randomly selected clinics from a pool of 42 in Harare will recruit 24 participants (N = 576). The clinics are randomised in a 1:1 ratio to receive either the intervention package [a problem solving therapy package delivered over a 4–6 week period by LHWs (N = 24) followed by a 6-week group support programme which focuses mainly on teaching a craft skill] or enhanced usual care, which includes usual care and psycho-education. Primary care attenders aged 18 years and above who score positive on a locally validated CMD screening questionnaire (Shona Symptom Questionnaire, SSQ-14) will be eligible for recruitment and asked for informed consent to participate in the trial. The primary measure is the SSQ score at 6 months.

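### The primary SSQ analysis adjusts for strata only; baseline SSQ, which every participant has, is left to a sensitivity analysis whose other covariates are not fixed

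*Protocol article*

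**What the plan says.** All in the protocol article.

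- **Primary model (Data analysis).** The difference in SSQ is estimated by "Linear regression of the mean score on strata and arm (2-way analysis of variance (ANOVA) on arm and strata"). No participant-level covariate enters.
- **Baseline checks (Data analysis).** "Comparability of participants in the two arms will be assessed for potential confounding factors, notably: age, sex, HIV status and SSQ score".
- **Adjusted analyses (Data analysis).** "Pre-defined sensitivity analyses includes adjustment for baseline SSQ score and other factors with imbalance (e.g. age, sex, HIV prevalence"). Baseline SSQ is named without condition. The other covariates depend on observed imbalance, the list is open, and no criterion for imbalance is given.
- **Allocation (Design).** Five strata were built from HIV status, housing density, clinic size and gender distribution. Allocation was further restricted for balance on HIV prevalence, clinic size, staff size and gender. Baseline SSQ is in neither set. Clinics were allocated before the trial began.
- **Entry (Inclusion criteria).** An SSQ-14 score of 9 or more is required, so baseline SSQ exists for everyone and lies between 9 and 14.
- **Blinding (Discussion).** Study coordinators are unblinded and involved in recruitment, though not in outcome assessment.

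**The concern.** The article treats baseline SSQ as a potential confounder, holds it for every participant, and still leaves it out of the headline estimate. Two things are at stake.

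- **Precision.** If baseline SSQ predicts 6-month SSQ, the primary confidence interval is wider than it need be.
- **Baseline differences.** With 12 clinics per arm, recruitment after allocation and unblinded staff taking part in it, the arms may differ in severity at entry. The strata-only estimate carries such a difference into the treatment effect. The confidence interval allows for the chance part but not for a systematic part.

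A smaller matter is that analyses called pre-defined include covariates to be picked after the data are seen. If adjusted and primary results diverge, nothing fixes which adjusted model should have been fitted.

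**Working it through.** **1. The plan's own figures.** Residual degrees of freedom: 24 clinics − 5 strata − 1 arm = 18. This matches the 18 that Data analysis gives for the risk comparison, and the SSQ model has the same terms.

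Sample size says that 24 clusters of 24 "provides 80% power to detect an effect size of 0.75, assuming a coefficient of variation (k) = 0.2 and 20% loss to follow-up". With two-sided 5% (assumed), 12 clinics per arm, 24 × 0.8 = 19.2 evaluable per clinic and the standard formula for unmatched clusters, in SD units:

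z = d / √(v/11) − 1.96, where v = 2/19.2 + k²(μ₀² + (μ₀ − d)²).

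This needs the control mean/SD ratio μ₀, which the section does not give. Back-solved, μ₀ = 3.3 fits: v = 0.104 + 0.04 × (10.89 + 6.50) = 0.800; z = 2.78 − 1.96 = 0.82; power 79.4%. The same value gives 91.9% and 91.6% for the two 90% scenarios. The pilot ratios do not reproduce 80%: 6.5/2.4 = 2.71 gives 92%, and 11.3/1.4 = 8.07 gives 20%. So 3.3 is an assumption.

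Its use here: within-clinic sampling is 0.104/0.800 = 13% of the variance. Explaining individual variation alone, with correlation 0.5, removes 0.25 × 13% = 3.3% of the variance, or under 2% of the SE. A larger gain requires clinic means at baseline to predict clinic means at 6 months.

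**2. Precision of the two-stage analysis.** Assumed inputs: baseline-to-6-month correlation r, and the same ICC for baseline and outcome. If r is equal at clinic and individual level, the ratio of adjusted to planned SE is about √(1 − r²). A simulation under no effect (24 clinics, 5 strata, 19 per clinic, 18 df, 4,000 runs per row) gave:

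| r | √(1 − r²) | ICC 0.05 | ICC 0.30 |
|---|---|---|---|
| 0 | 1.00 | 1.00 | 0.99 |
| 0.2 | 0.98 | 0.98 | 0.97 |
| 0.3 | 0.95 | 0.95 | 0.94 |
| 0.5 | 0.87 | 0.86 | 0.85 |

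The 0.99 at r = 0 is not a real gain; the slope is fitted to the same data. Type I error was about 4–6% for both methods.

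If baseline predicts only within clinics, the gain vanishes: 0.99–1.00 at r = 0.3. The least favourable case tried was r = 0.5 within clinics, none between, ICC 0.30. The pooled slope is 0.5 × 0.70 = 0.35. The adjusted variance is 0.30 × (1 + 0.35²) + 0.70 × (0.15² + 0.75)/19.2 = 0.365, against 0.30 + 0.70/19.2 = 0.336. The ratio is √(0.365/0.336) = 1.04, a small loss.

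**3. Size of a baseline difference.** Pilot SDs are 1.4 before and 2.4 after treatment (Background); assume r = 0.3.

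- Slope: 0.3 × 2.4/1.4 = 0.51 SSQ points per baseline point.
- SE of the baseline difference at ICC 0.05: 1.4 × √(2 × (0.05 + 0.95/24)/12) = 0.17, so the 95% limit is 0.34.
- Shift at that limit: 0.51 × 0.34 = 0.17 points, about 10% of 0.75 × 2.4 = 1.8 points. The 1.8 is derived, not stated in the article.
- At ICC 0.30 the limit is 0.64 and the shift 0.33 points, 18% of 1.8.
- For comparison, the SE of the 6-month difference at ICC 0.05 is 2.4 × √(2 × (0.05 + 0.95/19.2)/12) = 0.31, so the half-width is 2.10 × 0.31 = 0.65.

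A chance shift of 0.17 lies well inside that interval and is already counted in it. A systematic baseline difference converts at the same 0.51 per point and is not counted.

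**The case against.** The strongest case for the plan is that its primary model is a single, fully specified, valid stratified cluster-summary analysis. HIV and gender are already handled at clinic level by stratification and restricted randomisation. The baseline-adjusted analysis is promised anyway, so its place in the order is largely an efficiency preference. Attenders are invited by random number and a blinded research assistant administers the SSQ-14, which limits selective recruitment. All of this stands, and it rules out three stronger readings that a reader might infer:

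- **That the primary comparison is unadjusted.** It adjusts for strata.
- **That covariate choice is data-driven in the primary analysis, or inflates its error rate.** Choice by imbalance is confined to sensitivity analyses. In simulation the fixed primary model kept about 5% type I error. Picking the best of 16 models from four covariates would give about 10–20%, but the plan does not propose that.
- **That precision is known to be lost.** The article gives no correlation, and restricting entry scores to 9–14 tends to weaken it.

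It can also be argued that baseline adjustment costs a degree of freedom and pays only above a correlation of about 0.25. That holds for a clinic-level covariate added to the ANOVA (17 df, and a CI 3.5% wider at zero correlation). It does not hold for the two-stage method, which keeps 18 df.

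Finally, a fixed covariate list might be left to an unseen analysis plan. But the article does state a rule, and selection by observed imbalance sits badly with calling the analyses pre-defined.

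**Conclusion.** The point holds as an improvement, not as an error that invalidates the primary test. Leaving baseline SSQ to a sensitivity analysis may cost about 0–14% of the SE for an assumed correlation of 0–0.5 acting at both levels. At the half-width of 0.65 above, a 14% saving would bring it to about 0.56. There is no gain, and at worst among the cases tried a loss of about 4%, if baseline predicts only within clinics.

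The case does not rest on precision alone. Allocation did not balance baseline SSQ, and recruitment after allocation with unblinded coordinators makes a systematic difference possible, though nothing in the article shows that one will occur. Adjustment would address measured severity at entry, not every form of selective recruitment. The ICCs, correlations, alpha and mean/SD ratio are all assumptions.

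**What to change.** In Data analysis:

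- Make a two-stage cluster-summary analysis primary for SSQ. Stage 1 is an individual-level regression of 6-month SSQ on baseline SSQ, age, sex and strata, without arm. Stage 2 regresses the clinic mean residuals on arm and strata, with 18 df.
- Keep the strata-only ANOVA as a sensitivity analysis.
- Replace the clause on factors with imbalance by a fixed covariate list. Include individual HIV status only if it is recorded completely enough not to drop participants. The article lists HIV status for the baseline comparison but HIV prevalence for adjustment, and does not say how complete the individual data are.

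The cost is a change of analysis wording, made before outcome data are seen. Baseline SSQ comes from the entry screen, age and sex are already named for the comparability check, and the cluster-summary approach is kept.

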### Ethical issues

The study will be conducted according to regulations, guidelines and principles that have been endorsed at local and international levels. The protocol was approved by the Medical Research Council of Zimbabwe (MRCZ), Kings College London (KCL), and London School of Hygiene and Tropical Medicine (LSHTM).

## Discussion

The funding provided through Grand Challenges Canada has provided a unique opportunity to carry out a cluster randomized controlled trial of this promising intervention which has been running since 2006. The use of LHWs to address the treatment gap for mental, neurological and substance use disorders (MNS) particularly in LMIC has been recommended by the WHO [20]. Evidence from several LMIC indicates that this is feasible and cost-effective [7–9]. There is, however, a dearth of data on controlled trials in sub-Saharan Africa [21, 22]. This study will contribute to the much needed body of knowledge on the efficacy of psychological interventions delivered by LHWs in LMIC. Furthermore, the inclusion of a technological platform for both data collection and storage, as well as for support of the LHWs delivering the intervention, will give an opportunity to objectively assess the feasibility of supporting community health workers via e-health packages. With HIV now considered a chronic disease this trial will also look at the feasibility of using LHWs to address the issue of co-morbidity between HIV and MNS an approach that has been widely encouraged recently [23]. We hope to gain insight on this during analysis of our data as we expect to have a large population of PLWH in the study. Our study will be of interest to researchers involved in the development of psychological interventions for CMD in similar LMIC settings. It can also provide information on the feasibility of utilising the task-shifting approach promoted by the WHO.

Strengths of the study include the integration of three components (health, technological and income-generation) and the use of LHWs who are already integrated in a primary health care system that focuses on both communicable and non-communicable diseases. Moreover, the study will be innovatively addressing some of the most challenging barriers to mental health services, such as human resources, quality services, access to care facilities and medication as well as poverty. If successful, the results can be potentially scaled up to make a major contribution to improving access to treatment for CMD in Zimbabwe and secondly, it could possibly be adapted and applied across countries in the region. Weaknesses of the study include lack of blinding of some of the study team members, as is usual in a cluster randomised trial, particularly for the study coordinators who will actively be involved in the recruitment process although they will not play a role in the collection and assessment of outcome measures. Furthermore, the exclusion of people not residing in the geographical area of the clinic and those without valid national identification cards may exclude potential participants, however, this approach will minimise contamination and loss to follow up.

This trial offers an opportunity to show the effectiveness of a lay health worker driven intervention to address the treatment gap for CMD in LMIC. With screening and treatment of CMD at primary care level becoming routine, recognition of these problems will increase and effective help will potentially be made accessible, thereby reducing suffering and decreasing referral to tertiary level.

